### Part two: economic evaluation

The economic evaluation will involve both a cost-effectiveness analysis (CEA) and a cost-utility analysis (CUA). It will be performed from a societal perspective according to the intention-to-treat principle, using imputation to address missing data on the basis of the latest guideline for health-economic evaluation [71, 72]. All costs will be expressed in euro. Costs will be divided into one of three types: (1) main intervention costs in participating healthcare center; (2) mental healthcare utilization (e.g., medication, general practitioner, emergency care, outpatient visits to a general hospital, housing counseling, and admissions to a general hospital); and (3) costs stemming from productivity losses in paid work and volunteer jobs (both due to absenteeism and less efficiency while at work). Costs and outcomes will be evaluated at baseline, 9 and 18 months (parallel with the randomized trial).

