A structured method for reinforcing empowerment and social connectedness in mental healthcare is represented by the resource group method. In short, to constitute a resource group (RG), patients nominate significant others from their informal network (such as friends and family) and their formal network (such as a social worker or job-coach). During the frequent RG meetings, the RG discusses patients’ goals and wishes, and jointly determines a recovery plan to achieve them.

The first important characteristic of the RG method is that patients themselves take the lead in any decisions: they nominate the members of their RG, set their recovery goals and determine important aspects of how the RG meetings are designed [15]. Considering these decisions is a crucial factor in patients’ sense of autonomy and sense of ownership of their treatment. Patients are then encouraged to extend this to autonomy and ownership of their illness (such as their ability to cope with symptoms) and regarding other social and community aspects of life. This process of regaining control over one’s life—despite the need for support—is a key concept of empowerment, and is regarded as an important driving force in recovery [16, 17].

The second important characteristic of the RG method is that significant others are systematically engaged in treatment and care [18]. As a patient and his or her significant others form a team together with involved professionals, support in the recovery plan is broadened. Hereby, the fulfillment of a meaningful life and everyday activities is strengthened. In other words, through collaboration—joint discussion of patients’ wishes and needs, and creating space for sharing experiences and emotions—an empowered and supportive social environment can be built to supplement professional care. Having such environment in turn, is assumed to foster resilience and continuity in social and community integration. Improved integration and a feeling of connectedness are seen as facilitators and indicators of recovery [1, 19–21].

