*Recovery plan*: To prepare the RG meetings, the patient and case-manager will develop the recovery plan that is to be discussed during the RG meeting. This plan will comprise two long-term recovery goals, two short-term (i.e., 3-month) recovery goals, and a plan to recognize early warning signs (a “crisis plan”). The recovery goals will be formulated by the patient and can relate to all aspects of recovery, such as personal recovery (recovering identity); social rehabilitation (meaningful participation in society and social relationships); and health (improving physical and mental symptoms). In the crisis plan, patients will describe how others should recognize the personal early warning signs that indicate an approaching relapse, and how they want others to respond.

*Resource-group meetings*: RG meetings are usually scheduled once every 3 months, but the frequency may vary according to needs and wishes of the patient and the other RG members. The meetings will be structured clearly and consistently by an agenda that is determined by the recovery plan. The role of each member in accomplishing the recovery goal will be decided jointly by the RG, which will take shared responsibility for following the plan (shared decision making). The patient determines what the overall objectives of the RG meetings should be, and the group takes joint decisions on how they should be achieved [32, 33]. Between meetings, the patient, RG members and care professionals will work on the different parts of the recovery plan, using the next RG meeting to evaluate the steps they have taken. During these activities in between, the empowerment of the patient and the collaboration of the different RG members form the fundamental elements that shape the contact. Also, the crisis plan will be discussed during one of the first RG meetings. In the event of crisis or the need to prevent it, the aim is to enable RG members to provide the effective, adjusted guidance determined by the patient.

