#### Cost-effectiveness

##### Cost data and quality of life

The Trimbos and Institute of Medical Technology Assessment Cost Questionnaire for Psychiatry (TIC-P, interview) estimates use of care services, use of medication, and the amount of work loss (absenteeism and reduced efficiency) [66]. The questionnaire will be adapted to fit the purpose of this study and uses a 3-month recall period.

The 5-level EuroQol 5 dimensions (EQ-5D-5L) is a standardized non-disease-specific instrument that will be used to obtain utility scores on the basis of social tariffs, expressed in Dutch unit prices [67, 68].

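### The cost types give no place to informal care or the unpaid time of significant others, so the costs are narrower than the societal perspective claimed; the net direction of the effect is unknown

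*Protocol article*

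**What the plan says.** On perspective, the Protocol article (Part two: economic evaluation) states: "It will be performed from a societal perspective according to the intention-to-treat principle". The research question of that part asks, from the same perspective, whether adding RGs to FACT is preferable in costs, effects and utilities.

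On costs, the same section lists three types. The first two are given as: "Costs will be divided into one of three types: (1) main intervention costs in participating healthcare center; (2) mental healthcare utilization". The third is "costs stemming from productivity losses in paid work and volunteer jobs (both due to absenteeism and less efficiency while at work". The examples given in the text illustrate the second type only; the list of types is not open-ended.

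On measurement, the section Cost data and quality of life says that the TIC-P "estimates use of care services, use of medication, and the amount of work loss". It adds: "The questionnaire will be adapted to fit the purpose of this study and uses a 3-month recall period". What the adaptation contains is not stated.

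On the intervention, the Introduction names as the second main characteristic of RG that "significant others are systematically engaged in treatment and care". The section Resource group plus FACT describes an interview with each nominated member, meetings usually every 3 months, optional skills training, and work outside the meetings: "Between meetings, the patient, RG members and care professionals will work on the different parts of the recovery plan".

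**The concern.** A societal costing is expected to count resources whoever supplies them. Here the method under test deliberately changes how much time family and friends put in, and that resource is missing from the list of costs. The plan counts the staff time spent on RG and any saving in professional care, but not the unpaid time that accompanies them.

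What is at stake is the second study objective (cost-effectiveness and cost utility). An ICER built from these cost types answers a healthcare-plus-productivity question while being reported as the answer to a societal one. The primary comparison on the NEL is not affected.

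**Working it through.** **Step 1. Does any cost type or instrument hold this resource?** The protocol gives no cost, hour count, unit price or ICER, so there is no figure to reproduce. The check sets the sections side by side.

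- *Intervention costs in the centre:* tied to the provider. A relative's evening at a meeting is not a cost of the centre.
- *Care utilization:* the examples are medication and professional services. Informal care is not among them.
- *Productivity losses:* defined through absence from, or lower efficiency in, paid or volunteer work. Whose work is not said, so paid work lost by relatives is not expressly excluded. The only source described, however, is the participant's own TIC-P interview. Unpaid time fits neither absence nor lower efficiency at work.
- *TIC-P as described:* care services, medication and work loss. No informal-care item is named.
- *IEQ:* the only instrument in Table 3 that significant others complete. It measures burden, is listed apart from the economic evaluation, and is not carried into the costs.

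Unpaid time of significant others therefore has no place in the costing as written.

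**Step 2. How large could the RG-specific part be?** Only the meeting interval comes from the protocol: 18 months / 3 months = 6 meetings, a nominal count because the frequency may vary and meetings may be delayed. All other inputs are assumptions.

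Hours = members x (6 x hours per meeting + 1 h interview) + members x monthly hours between meetings x 18. Cost = hours x hourly value.

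| Case | Informal members | Hours per meeting | Hours per month between meetings | EUR per hour | Hours | EUR per RG patient |
|---|---|---|---|---|---|---|
| None | 0 | – | – | – | 0 | 0 |
| Low | 1 | 1.5 | 0 | 10 | 1 x (9 + 1) = 10 | 100 |
| Middle | 3 | 2 | 1 | 15 | 3 x (12 + 1) + 3 x 18 = 93 | 1,395 |
| High | 5 | 3 | 2 | 20 | 5 x (18 + 1) + 5 x 36 = 275 | 5,500 |

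The zero row is a documented case. Resource group plus FACT allows a minimal group of patient, case manager and psychiatrist, and the Discussion accepts that a patient may nominate professionals only.

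**Step 3. What would that do to the ICER, with nothing else changing?** Shift = omitted cost / QALY gain. At an assumed gain of 0.05 QALY:

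- Low: 100 / 0.05 = EUR 2,000 per QALY
- Middle: 1,395 / 0.05 = EUR 27,900 per QALY
- High: 5,500 / 0.05 = EUR 110,000 per QALY

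At a gain of 0.02 these become 5,000, 69,750 and 275,000; at 0.10 they become 1,000, 13,950 and 55,000.

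**Step 4. What would cancel it?** Informal care outside the RG is also uncounted, in both arms. The added RG time is offset if other informal care per RG patient falls by hours / 78 weeks (18 months), summed over all significant others:

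- Low: 10 / 78 = 0.13 h per week
- Middle: 93 / 78 = 1.19 h per week
- High: 275 / 78 = 3.53 h per week

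A larger fall reverses the sign. The Introduction expects that professional support may lower the burden on significant others, so such a fall is within what the protocol itself considers possible.

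**The case against.** The strongest reply concerns direction. A reader might infer that the ICER is biased in favour of RG, with the omission falling almost wholly on one arm. The documents do not support this. Informal care is uncounted in both arms, and standard FACT also involves the network (Table 1: a contact person, family who can be invited, contact in a crisis). Burden may fall under RG, and some RGs may have no informal members. What matters is the net difference between arms, which the documents do not give. This part of the reply stands in full.

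A second reply is that detail is unseen: the TIC-P will be adapted, the third cost type does not say whose losses count, and the plan refers to a health-economic guideline, sensitivity analyses and CHEERS. This stands in part, since lost paid work of relatives might be included. It does not remove the point. An informal-care item in the questionnaire would still have no cost type to enter, and a sensitivity analysis cannot vary a quantity that was not collected.

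A third reply is the protocol's remark that RG members bear no costs. It stands beside the description of the skills training and does not address the value of members' time.

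It is also too strong to say that the method moves work from paid staff to relatives, or that the research question cannot be answered. The Introduction describes the network as an addition to professional care and only hopes for later independence from it. RG also adds staff work, which the first cost type can hold. With a narrower label, the planned analysis answers a narrower question properly.

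**Conclusion.** The point holds as a conflict between the stated perspective and the stated cost types. Followed as written, the plan yields an ICER narrower than societal, and the missing resource is one that RG changes by design.

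The gross value of the added RG time lies between EUR 0 and about EUR 5,500 per RG patient under the assumptions in the working. This illustrates scale and does not measure bias. Considered alone, that time would understate RG costs. Once a possible fall in other informal care is allowed for, the net direction is unknown. The plan should correct this because a stated objective depends on it, but the clinical effectiveness analysis is untouched.

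**What to change.** Add a fourth cost type: informal care and time of significant others, measured once and in the same way in both arms. Either of two forms will do:

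- one hours item in the adapted TIC-P that includes any RG meeting and task time; or
- the same item with RG meeting time expressly excluded, and meeting time taken from the RG meeting form. That form records the members, but duration is not among its described contents, so a duration item would be needed.

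The exclusion in the second form matters: without it, meeting time is counted twice and the result tilts against RG. Value the hours at a standard hourly price, vary that price in sensitivity analysis, and report the ICER with and without this cost type.

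If the time is not collected, relabel the perspective as healthcare plus productivity, in the research question as well, and restrict the conclusion to that.

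The cost is one or two items, a unit price, a slightly longer assessment and some recall error in the reported hours. Relabelling costs nothing in data collection but gives up the societal claim.

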#### Research question

From a societal perspective, is the addition of RGs to FACT preferable to FACT alone in terms of costs, effects and utilities?

#### Analysis

At baseline, the homogeneity of groups will be assessed with regard to both costs and outcomes. Where necessary, we will control for baseline differences [73, 74]. The primary outcome parameter for the CEA will be treatment response after 18 months, which is defined as within-patient pre-post increase in empowerment (NEL). For the CUA, we will convert the health states resulting from the five dimensions of the EQ-5D-5L into utilities based on the Dutch tariffs of the EuroQol, the so-called EQ-5D value set [68]. Using the area under the curve (AUC) method, the periods between the assessments will be weighted by these computed utilities. This will allow quality-adjusted life years (QALYs) to be adjusted over the entire trial period. Similarly, cumulative costs over the entire follow-up period will be obtained from the cost estimates at the various assessments [67, 75]. The total QALYs gained during 18 months is the primary outcome of the CUA.

Incremental cost effectiveness ratios (ICERs) will be calculated for both CEA and CUA: ICER = (C1 − C2)/(E1 − E2), where C refer to costs, E to effects, and subscripts (1 and 2) to the two trial conditions (RG + FACT/standard FACT). These ICERs express the average incremental costs associated with 1 additional unit of the measure of effect [76]. For the CEA, this refers to the incremental costs per treatment responder (= increase at the NEL); for the CUA, it is the incremental costs per QALY gained. Next, confidence intervals around the ICER will be computed using a nonparametric bootstrap approach: > 2500 non-parametric bootstrapped samples will be extracted from the original dataset. For each of the bootstrapped samples, the incremental costs, incremental effects, and the incremental cost-effectiveness ratio (ICER) will be calculated. The point estimates of the mean ICER and the resulting > 2500 ICERs will be used for further calculation, and will be graphically displayed in a cost-effectiveness plane [76]. Sensitivity analyses will be performed to assess the robustness of the findings. When conducting the analyses and describing the results, we will follow the CHEERS guideline for health-economic evaluations [77].

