#### Sample size

Power calculations of the study will be based on the earlier described meta-analysis investigating the effectiveness of RACT [31]. Using the program G*power (two-sided, power = 80%, alpha = 0.05; G*power 3.1) with a medium effect size (*d* = 0.5) [31], we found that a total of 126 participants would be sufficient to detect a statistically significant difference between the two conditions. If account is taken both of repeated measures within a person (assuming a within-correlation of 0.6) and of clustering of data (teams; assuming an intraclass correlation coefficient (ICC) of 0.05, health centers; assuming an ICC of 0.1), a sample of N = 133 is needed. To account for possible drop-outs (rate 35%), we aim to recruit a total sample of N = 180. Eighteen teams at a total of nine Dutch mental health centers will participate, each with two teams. In principle, each team should deliver a mean of N = 10 patients per team over the course of 1 year.

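### The planned bootstrap confidence interval on the ICER cannot be interpreted when the incremental effect is not clearly different from zero, and "mean ICER" is ambiguous

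*Protocol article*

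**What the plan says.** The protocol article, Part two (economic evaluation), Analysis, defines the ICER as (C1 − C2)/(E1 − E2). It applies this to two effects: response at 18 months, meaning a rise in a patient's NEL score from baseline (CEA), and QALYs over 18 months (CUA). It then states that "confidence intervals around the ICER will be computed using a nonparametric bootstrap approach". More than 2500 samples are drawn, and incremental costs, incremental effects and the ICER are calculated in each. The next sentence begins "The point estimates of the mean ICER and the resulting" and continues with the 2500-plus bootstrapped ICERs. These are to go into further calculation and onto a cost-effectiveness plane. Sensitivity analyses and CHEERS reporting are also promised.

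The interval is planned unconditionally for both analyses, and no rule is given for replicates that fall in different quadrants of the plane.

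**The concern.** The ratio is discontinuous where the effect difference is zero. A replicate with a tiny positive effect difference gives a huge ratio, and one with a tiny negative difference gives a huge ratio of the opposite sign. Sign alone does not identify the quadrant. A negative ICER is either dominant (cheaper, more effect) or dominated (dearer, less effect). A positive one is either north-east (dearer, more effect) or south-west (cheaper, less effect). If the replicates spread over several quadrants, sorting the ratios from low to high does not sort them from good to bad, and the 2.5th and 97.5th percentiles do not bound anything a decision maker can use. An average of such ratios is driven by the few replicates closest to zero effect.

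At stake is the answer to the economic research question, whether adding resource groups to FACT is preferable in costs, effects and utilities. The primary effectiveness conclusion is not affected.

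**Working it through.** **Inputs from the protocol article (Sample size; Study design).** "two-sided, power = 80%, alpha = 0.05"; d = 0.5, introduced "with a medium effect size"; "assuming a within-correlation of 0.6"; 180 recruited, allocated 1:1, so 90 per arm; drop-out 35%, so 180 × 0.65 = 117 with data.

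**Inputs that are assumptions.** The article gives no QALY or cost difference and no SDs. QALY effects are therefore taken as d = 0.1 to 0.5. Where money is needed: QALY SD 0.3, cost difference EUR 2,000, cost SD EUR 30,000, costs and QALYs independent and normal. Clustering is ignored throughout.

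**Step 1. Reproduce the plan's figure.** n per arm = 2(1.960 + 0.842)²/0.5² = 62.8, so 63 per arm and 126 in total, matching "a total of 126 participants would be sufficient". (The t-test version gives 128.)

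**Step 2. How often does the 95% interval for a QALY difference include zero?** With z = d/√(2/n), the probability is Φ(1.96 − z) − Φ(−1.96 − z). For n = 90, √(2/90) = 0.149. For 117 in total, n = 58.5 and √(2/58.5) = 0.185.

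| Assumed d | z (N = 180) | Includes zero, N = 180 | Includes zero, N = 117 |
|---|---|---|---|
| 0.1 | 0.67 | 90% | 92% |
| 0.2 | 1.34 | 73% | 81% |
| 0.3 | 2.01 | 48% | 63% |
| 0.5 | 3.35 | 8% | 23% |

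If the estimate equals the assumed effect, the share of replicates below zero is Φ(−z): 25% at d = 0.1 and 9% at d = 0.2 for N = 180.

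**Step 3. The same for the NEL-responder CEA.** With within-person correlation 0.6, the SD of change in baseline SD units is √(2(1 − 0.6)) = 0.894. Response probabilities are Φ(m/0.894) in control and Φ((m + d)/0.894) in the RG arm, where m is the mean control change, taken as 0 to 0.4.

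- d = 0.5, m = 0: 0.500 against 0.712. SE = √[(0.500 × 0.500 + 0.712 × 0.288)/90] = 0.071, z = 2.98, includes zero in 15%.
- d = 0.5, m = 0.4: 0.673 against 0.843. SE = 0.063, z = 2.72, includes zero in 22%.
- d = 0.5 with 117 patients: 33–41%.
- d = 0.3: 57–61% with 180 and 70–73% with 117.

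**Step 4. What the ratios look like in one assumed case.** QALY difference 0.03 (d = 0.1), cost difference EUR 2,000, 90 per arm. The ratio of mean differences is 2,000/0.03, about EUR 66,700 per QALY. Of the bootstrapped ratios, 41% were negative, made up of about 25% dominant and 17% dominated. The positive ones were about 50% north-east and 8% south-west. Five sets of 2,500 replicates gave averages of about −265,000, −97,000, −32,000, +8,000 and +63,000, with percentile intervals running from roughly minus one million to plus one million euro.

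**Step 5. If "mean ICER" is an average of ratios.** In 300 simulated trials per setting (90 per arm, 2,501 resamples), the average differed from the ratio of mean differences by more than 50% in 73%, 62%, 44% and 21% of trials at d = 0.1, 0.2, 0.3 and 0.5. It had the opposite sign in 31%, 23%, 13% and 4%.

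**The case against.** Four points can fairly be made for the plan.

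- **The mean.** A reader might infer that the plan averages the bootstrapped ratios. The text does not establish this. The ICER is defined beforehand as a ratio of differences, and the sentence lists the point estimate and the replicates as two objects, so the ratio of mean differences is a natural reading. This stands: the wording is ambiguous, and Step 5 applies only under the less favourable reading. The interval on the ICER is explicit under either.
- **Likelihood.** A reader might infer that crossing zero is the expected case here. The documents do not show that. At the planned d = 0.5 the responder analysis is clear of zero in most trials, and for QALYs the answer depends on an effect that the article does not state. This stands too. However, d = 0.5 comes from comparisons with care as usual in psychotic disorder, the article says no earlier study compared RG head-to-head with FACT, and it expects possible spillover into the control condition. A smaller effect is therefore a case the plan should handle.
- **Validity.** Under-coverage would be the wrong charge. The percentile interval covered the true ratio in 97–99% of simulated trials with 90 per arm. Its fault is that it is very wide and mixes quadrants. The plane makes that spread visible, but an interval printed beside it would still be hard to read.
- **Missing detail.** Net benefit, acceptability curves and the resampling scheme may be in a fuller plan. Their absence from a condensed article is no fault. In particular, the silence on resampling within arm and team is not a finding, and requiring it would bring its own problem: about ten patients per team at 1:1 gives cells of about five, where an ordinary bootstrap shrinks the variance by 4/5. Costs and effects are already resampled together. What remains is a rule that the article does state, an unconditional interval on the ratio.

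**Conclusion.** The concern holds for the unconditional confidence interval on the ICER in both analyses, and for the unclear term for the point estimate. The interval loses its meaning whenever the incremental-effect distribution reaches zero.

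For the CUA this happens in anything from about 90% of trials (assumed d = 0.1) to 8% (d = 0.5) with 90 per arm. For the responder CEA at the protocol's own effect it is a minority case, about 15–22%, rising to 33–41% if only 117 patients contribute. Because imputation is planned, the figures for 180 may be closer to what is analysed. All of these use normal approximations without clustering, and the QALY effects are assumptions.

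The documents do not support saying that the whole bootstrap is invalid, that the ICER will certainly be averaged over replicates, or that failure is the expected outcome. This is a correction worth making to a secondary analysis.

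**What to change.** 1. State that the point ICER is the ratio of the mean cost difference to the mean effect difference, and not the mean of the bootstrapped ratios.
2. From the same replicates, report incremental net monetary benefit, λ(E1 − E2) − (C1 − C2), with 95% intervals over a pre-stated range of willingness-to-pay values λ; a cost-effectiveness acceptability curve; and the percentage of replicates in each quadrant of the plane.
3. Report a confidence interval for the ICER only when the interval for the incremental effect excludes zero. Otherwise give the point ratio, if at all, with the quadrant shares.

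The cost is a change of wording and a little more reporting. No new data and no new resampling are needed. The price is that results depend on the chosen willingness-to-pay range. That range has to be fixed in advance for both effect scales, per QALY and per additional NEL responder.

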### Part one: effectiveness study

#### Study design

Patients in this multisite RCT will be randomly allocated either to RG method plus FACT or to standard FACT (ratio 1:1). Randomization will be performed at individual patient level. Data for both conditions will be collected at baseline and after 9 and 18 months (follow-up assessments). For an overview of the flow of screening procedures and assessments, see Fig. 1. Importantly, since FACT teams do almost all outpatient care in the Netherlands for SMI patients, it was not possible to have a second control group without FACT.

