##### Randomization and blinding

Randomization will be performed on an individual level. A statistician from the Trimbos Institute, who will be independent from the research team, will perform the randomization using a computer-generated concealed-randomization sequence stratified on teams. To keep randomization unpredictable, the sequence will contain variable-allocation block sizes [37], in which two sizes of allocation blocks (i.e., 2 and 4) are randomized. Assuming ten participants per team, this results in three possibilities for block size 4 (i.e., 2 × 4; 1 × 4; 0 × 4). To minimize the risk of imbalance between conditions, the ratio of these sequences will be stratified on respectively 1:2:2. The allocation sequence will be stored by the independent statistician and be concealed from all researchers, care providers and participants. Participants will be allocated after baseline measurement. Once they have been allocated, the researcher and local staff will be informed of the condition by email. Further matching between patient and case-manager will be performed by the local FACT team staff and will be based on condition. That is, when participants are allocated to the RG condition, care providers trained in the RG procedures will be the case-manager. Patients in the control condition can have any FACT care providers as their case-manager.

Assessments comprise self-report questionnaires, and structured and semi-structured interviews (see Table 3). They will take place at the participants’ homes or any other location they prefer. An independent and blinded interviewer will guide them through the self-report questionnaires and will conduct the interviews. The interviewer will bring a laptop and- using a unique login-code- will assess the questionnaires online, then securing them on an encrypted server (Jambo). If participants are unable to use the laptop, they will fill in the questionnaires on paper and the interviewer will then later enter the data into the online environment.

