#### Analyses

Outcome data will be analyzed using multilevel mixed regression models with 4 levels: observations within people, people within teams, and teams within centers. Analyses will be conducted on the entire randomized sample (i.e., intention to treat). Supplementary analysis will be done on the completers sample. A completer will be defined after further inspection of the frequency of the RG meetings to define a minimum of attendance of a RG meeting during a 12-month period after the first assessment. In future publications the number of minimum RG meetings will be clearly stated within the definition of a completer and included in the consort flow chart of the RCT. To analyze potential between-condition differences in baseline characteristics (such as gender and diagnosis), we will use Student’s t-tests for continuous variables and Pearson Chi-squared tests for categorical variables. As a covariate, the analysis will include variables that show different distributions in the conditions (p ≥ 0.05 difference at baseline) and are correlated with the results. For categorical outcome variables we will choose counts and, if there are non-normal residuals, appropriate forms of mixed regression (such as binomial, Poisson and gamma). All analyses will be carried out using SPSS version 20+ and/or R version 3.0+. Results will be described in accordance with the CONSORT guidelines for randomized controlled trials [35].

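### As written, the economic bootstrap has no term for the team strata of the randomisation; if the arm effect is constant across teams, its intervals are modestly too wide

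*Protocol article*

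**What the plan says.** Protocol article, Randomization and blinding: patients are allocated individually "using a computer-generated concealed-randomization sequence stratified on teams", and "two sizes of allocation blocks (i.e., 2 and 4) are randomized". Study design gives a 1:1 ratio.

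Protocol article, Analyses (Part one): outcomes are analysed with "multilevel mixed regression models with 4 levels", which include team and centre.

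Protocol article, Part two, Analysis: the ICER is defined as the difference in costs over the difference in effects between the two conditions. For its interval, "> 2500 non-parametric bootstrapped samples will be extracted from the original dataset", and then "For each of the bootstrapped samples, the incremental costs, incremental effects, and the incremental cost-effectiveness ratio (ICER) will be calculated". No team or centre term, stratified resampling or regression is named. Adjustment is foreseen only for baseline imbalance, if it proves to be needed. The introduction to Part two specifies intention to treat with imputation of missing data.

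Protocol article, Sample size: the clustering assumptions are "teams; assuming an intraclass correlation coefficient (ICC) of 0.05, health centers; assuming an ICC of 0.1". No ICC is given for costs, QALYs or NEL response.

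**The concern.** Blocking within team keeps the two arms nearly equal inside every team. Whatever makes one team or centre more costly or better-scoring than another then falls on both arms alike and drops out of the arm contrast. A bootstrap that resamples patients without regard to team lets the team mix drift apart between the arms. The spread of the bootstrap replicates therefore contains between-team and between-centre variance that the real estimate does not have.

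At stake is the width of the intervals for incremental costs and incremental effects, and hence the spread on the cost-effectiveness plane. The increments themselves are not at stake. Part one accounts for the team structure, while Part two, as written, does not.

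**Working it through.** **Inputs.**
- Sample size: 18 teams, two in each of 9 centres, a mean of 10 patients per team, 180 in total, dropout 35%.
- Randomization and blinding: blocks of 2 and 4. A list of ten made of complete blocks (two 4s and one 2, one 4 and three 2s, or five 2s) gives exactly 5:5 per team, so 90 per arm.
- ICCs of 0.05 (team) and 0.10 (centre), read as shares of a total variance of 1: vt = 0.05, vc = 0.10, ve = 0.85. Their use for costs, QALYs and NEL response is an assumption.

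**The plan's own figure.** The article states no standard error for the economic evaluation, so there is none to reproduce on this point. Its unadjusted sample size does reproduce: 2 × (1.960 + 0.842)² / 0.5² = 62.8, so 63 per arm and 126 in total.

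**1. True standard error, constant arm effect.** Team and centre cancel, leaving √(2 × ve / 90) = √(2 × 0.85 / 90) = 0.137.

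**2. Plain bootstrap, patients resampled within arm.** Each arm has 90 patients in 18 teams and 9 centres, so the expected variance is (2/90) × [ve × 89/90 + vt × 17/18 + vc × 8/9].
- In brackets: 0.8406 + 0.0472 + 0.0889 = 0.9767.
- Standard error: √(0.9767 × 2/90) = 0.147.
- Ratio to the truth: √(0.9767 / 0.85) = 1.072, about 7% too large.

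**3. Smaller ICC.** With vt = 0.05, vc = 0 and ve = 0.95, the bracket is 0.9394 + 0.0472 = 0.9867, and √(0.9867 / 0.95) = 1.019, about 2%. Ignoring the finite-sample factors gives 1/√0.95 = 1.026.

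**4. Simulation with ICCs 0.05 and 0.10.**
- All 180 analysed: plain bootstrap 0.147 against 0.140 in one run (ratio 1.05), and 0.146 against 0.137 in another (1.07). In the second run the team-adjusted bootstrap gave 0.138.
- 35% dropout, complete cases: plain bootstrap 0.182 against 0.1765 (1.03). The team-adjusted estimate had a true standard error of 0.177, so adjustment gained nothing in precision.
- 35% dropout with a team ICC of 0.05 only: ratio 1.02.

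**5. Resampling only within team-by-arm cells.** With five patients per cell the variance shrinks by 4/5: √(0.85 × 0.8 × 2/90) = 0.123 against 0.137, about 11% too small.

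**6. If the arm effect varies by team.** Assume a component added in one arm and subtracted in the other, with variance share vx taken from the residual. The true variance is 2 × ve/90 + 4 × vx/18.
- vx = 0.02, ve = 0.83: √(0.01844 + 0.00444) = 0.151.
- vx = 0.05, ve = 0.80: √(0.01778 + 0.01111) = 0.170.
- The plain bootstrap stays near 0.147: about 3% and 13% too small (0.147/0.151 and 0.147/0.170).
- A team-adjusted standard error stays near 0.138: about 9% and 19% too small (0.138/0.151 and 0.138/0.170).

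**The case against.** The strongest objection is that this is read from silence in a condensed article. The ICER formula is the generic definition and does not say how costs and effects are estimated. The resampling details may well be left to a fuller plan. A reader might infer that the sponsor has decided to compare raw arm means and discard the strata; the article does not say so. What remains is that the section does set out its procedure, and its one route to adjustment depends on observed imbalance. Team is balanced by design, so that route would not bring it in.

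Three other strong readings are not supported.
- That the CEA must then disagree with the trial's own NEL result because teams are left out. Part one analyses the NEL total score over repeated observations; the CEA uses a pre-post response at 18 months. They are different measures and need not agree in any case. A pre-post measure has also already shed part of any stable team level.
- That about 13% of the information is thrown away (1 − 0.85/0.9767 = 0.13, or 23 of 180 patients). With 5:5 teams the plain and team-adjusted differences in means are the same number; only the reported standard error is inflated. The figure also needs the borrowed ICCs and complete data.
- That the intervals are certain to be too wide, and that adjusting for team has no drawback. Both depend on a constant arm effect. The RG method is delivered by a few trained case-managers in each team, so some variation by team is plausible, and step 6 shows both standard errors are then too small, the adjusted one more so.

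The objection that dropout shrinks the excess is right for a complete-case analysis. It has less force here, because Part two specifies intention to treat with imputation, which can keep all 180 patients in.

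**Conclusion.** The point holds in a modest form. As written, the economic bootstrap carries no term for the strata on which patients were randomised. With a constant arm effect, the intervals for incremental costs and effects are about 5–7% too wide when the ICCs are 0.05 and 0.10 and all 180 patients are analysed. The excess is about 2–3% with a total ICC of 0.05, or with 35% complete-case dropout. The ICCs are assumed for all three bootstrapped outcomes. The excess is likely smallest for NEL response and larger for cumulative costs and QALYs, which retain team-level differences. The error is conservative under that assumption, leaves the point estimate unbiased and does not touch the primary analysis. This is an optional improvement.

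**What to change.** State in Part two, Analysis, that patients are resampled within arm with each patient's costs and effects kept together, and that in every bootstrap sample the incremental costs and effects are estimated from a model with arm and the team strata. Since teams are nested in centres, team indicators also absorb centre. Do not resample only within team-by-arm cells: at about five patients each, that understates the standard error by about 11%.

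The cost is one regression step per bootstrap sample and a sentence of text; no new data are needed. State the limits alongside it. There is little to gain if many patients are lost and not imputed. The inference is conditional on the participating teams: if the arm effect varies between teams, the standard error does not cover that variation, and the plain bootstrap does not properly cover it either.
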